**Methods and analysis:**

The eHealth DIabetes remission Trial is a multicentre, two-arm, non-inferiority, open-label, randomised controlled parallel group trial with blinded endpoint assessment conducted at two centres in Sweden. The study duration is 2 years. People with type 2 diabetes (≤6 years duration) use total diet replacement (approximately 900 kcal/day) with the aim of losing 15 kg and achieving diabetes remission. Participants are randomly assigned to either the eHealth support group or the face-to-face support group. The treatment programme to achieve and maintain weight loss is the same in both groups, but the method of support differs between the groups. The primary outcome is haemoglobin A1c (HbA1c) after 1 year. The secondary outcome is HbA1c at 6 months and 2 years. Other important secondary outcomes are diabetes remission rate, body weight and cost-effectiveness. The latter is assessed using the incremental cost per quality-adjusted life-years gained.

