### Objective

Our primary hypothesis is that eHealth support is non-inferior to face-to-face support in helping patients with type 2 diabetes achieve remission through calorie restriction. Our secondary hypothesis is that eHealth support will be more cost-effective than face-to-face support.

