### Primary outcome

The primary outcome is HbA1c as a continuous outcome at 12 months.

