### Secondary outcomes

The primary outcome HbA1c as a continuous outcome at 6 and 24 months.Incremental costs per quality-adjusted life-years (QALY) gained (at 24 months only).Incremental costs per diabetes remission (at 24 months only).Estimated lifetime costs (at 24 months only).Diabetes remission rate (proportion of participants with HbA1c<48 mmol/mol (<6.5%) without diabetes medication).Body weight and BMI.Reduction in body weight by at least 15 kg (proportion of participants).Waist circumference.Abdominal height.Blood pressure measured at the research facilities.24 hours blood pressure home monitoring.Plasma lipid profile.Plasma liver enzymes.Fasting blood glucose.Plasma glucose 120 min after the OGTT.Daily steps (measured with activity tracker).Quality of life (EuroQol Quality - 5 Dimensions - 5 Levels (EQ-5D-5L)).Quality of life (Brunnsviken Brief Quality of Life Scale).Estimation of own health (36-Item Short Form Survey (SF-36)).Relation to food (three-factor eating questionnaire).Estimation of exhaustion (Karolinska Exhaustion Disorder Scale).Eating habits (food frequency questionnaire 2020).Study experience (written answers to open questions, at 24 months only).Number of prescribed antidiabetic medications.Number of prescribed antihypertensive medication.Number of participants that discontinue the intervention.Long-term follow-up after study completion of HbA1c, body weight, blood pressure, diabetes complications, and usage of antidiabetic and blood pressure medication.

All secondary outcomes are assessed at 6, 12 and 24 months if not otherwise stated above. A description of other pre-specified outcomes can be found on *ClinicalTrials.gov* (NCT05491005).

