### Statistical analyses

For the primary outcome, the continuous variable HbA1c is analysed for non-inferiority using ANCOVA, with HbA1c at 12 months as the dependent variable and the group as the independent variable. The analysis will be adjusted for baseline HbA1c and study centre to account for stratified randomisation. The non-inferiority margin is 8 mmol/mol (0.8%). If a participant is taking medication to lower blood glucose, that participant’s HbA1c will be adjusted for the average blood glucose-lowering effect of the medication used, according to the meta-analysis by Tsapas and colleagues.^29^ The analysis is performed according to the intention-to-treat principle with imputation of missing values using multivariate imputation by chained equations.^31^ The same analysis will be performed on the full analysis set, that is, all randomised participants with HbA1c measurements at baseline and 12 months, as a sensitivity analysis. The intention-to-treat population is defined as all study participants that were randomised.

The secondary outcome diabetes remission in per cent will be tested for non-inferiority with a non-inferiority margin of 10 percentage points, followed by a test for superiority. The other secondary outcomes will be tested for superiority only.

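### HbA1c at 24 months falls under superiority-only testing, so the plan has no pre-specified, adequately powered non-inferiority test at 2 years

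*Protocol article*

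**What the plan says.** The article's Primary outcome section fixes the time point: "The primary outcome is HbA1c as a continuous outcome at 12 months". In Statistical analyses, HbA1c is "analysed for non-inferiority using ANCOVA, with HbA1c at 12 months as the dependent variable", with a margin of 8 mmol/mol.

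HbA1c at the other two visits is secondary. The first item under Secondary outcomes is "The primary outcome HbA1c as a continuous outcome at 6 and 24 months", and the Abstract says: "The secondary outcome is HbA1c at 6 months and 2 years".

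For the secondary outcomes, Statistical analyses gives two rules:

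- Remission has its own rule: "The secondary outcome diabetes remission in per cent will be tested for non-inferiority with a non-inferiority margin of 10 percentage points, followed by a test". The second test named there is one of superiority.
- Every remaining secondary outcome falls under a general rule: "The other secondary outcomes will be tested for superiority only".

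The Objective section is framed as non-inferiority: "Our primary hypothesis is that eHealth support is non-inferior to face-to-face support in helping patients with type 2 diabetes achieve remission through calorie restriction". The Abstract adds: "The study duration is 2 years". Remission has no exception to the general 6-, 12- and 24-month schedule under Secondary outcomes, so its non-inferiority test is read here as applying at 24 months too.

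**The concern.** Read as written, the two rules send HbA1c at 24 months to a superiority test. The hypothesis is that eHealth support is not materially worse, and a superiority test does not answer that. If the arms are equal it is non-significant about 95% of the time, and non-significance is not evidence of non-inferiority.

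The plan also runs against its own reasoning. Sample size and justification prefers continuous HbA1c to dichotomous remission for investigating non-inferiority. At 24 months the stated rules do the reverse: remission keeps a non-inferiority test and HbA1c loses it.

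At stake is the 2-year statement. The weight maintenance phase runs to week 104 and cost-effectiveness is judged at 24 months, so the economic result would have no adequately powered clinical non-inferiority test at the same time point. Timing matters as well. The Publication plan has the primary outcome published once all participants reach 12 months, and a 24-month non-inferiority test added after that would be post hoc and contrary to the published rule.

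**Working it through.** **Inputs from the article.** Margin 8 mmol/mol, SD 13.3 mmol/mol, alpha 0.05, power 90%, 96 participants before and 106 after a 10% drop-out allowance (Sample size and justification); 1:1 allocation (Randomisation); remission margin 10 percentage points (Statistical analyses); 36% remission at 2 years in the earlier face-to-face trial (Introduction).

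**Assumptions.** The article gives no SD or missing rate for 24 months. I use SD 13.3, no gain from covariates, no true difference, and 8% to 30% missing out of 106.

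**1. The plan's own figure.** n per arm = 2 × SD² × (z_α + z_β)² / margin².
- One-sided 0.05: 2 × 13.3² × (1.645 + 1.282)² / 8² = 47.4, so 48 per arm and 96 in total. This matches. A t-based calculation gives 98.
- One-sided 0.025: 2 × 13.3² × (1.960 + 1.282)² / 8² = 58.1, so 59 per arm and 118 in total. This does not match.
- Drop-out: 96 × 1.1 = 105.6, giving 106 (96 / 0.9 = 106.7 would give 107).

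The article does not state sidedness; its figure corresponds to one-sided 0.05. Both levels are shown below.

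**2. 24-month HbA1c as now planned (two-sided 0.05 superiority).** With 10% missing there are 106 × 0.9 / 2 = 47.7 per arm, and SE = 13.3 × √(2/47.7) = 2.72. Power ≈ Φ(difference/SE − 1.96):
- 2 mmol/mol: 11%
- 4 mmol/mol: 31%
- 8 mmol/mol: 84%

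**3. 24-month remission non-inferiority.** SE = √(2 × 0.36 × 0.64 / n); power = Φ(0.10/SE − z).
- 53 per arm (no loss): SE = 0.0932. Φ(1.072 − 1.645) = 28%; Φ(1.072 − 1.960) = 19%.
- 42 per arm (about 20% loss, assumed): SE = 0.1047. Φ(0.955 − 1.645) = 25%; Φ(0.955 − 1.960) = 16%.

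**4. 24-month HbA1c non-inferiority, margin 8 (noncentral t).** Noncentrality = 8 / (13.3 × √(2/n)).

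| Missing | n per arm | One-sided 0.05 | One-sided 0.025 |
|---|---|---|---|
| 8% | 48.8 | 90% | 84% |
| 10% | 47.7 | 90% | 83% |
| 15% | 45.0 | 88% | 81% |
| 22% | 41.3 | 86% | 77% |
| 30% | 37.1 | 82% | 72% |

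At the same 42 per arm as in step 3, the normal approximation gives Φ(8/2.902 − 1.645) = 87% at one-sided 0.05 and 79% at 0.025. If eHealth is truly 2 mmol/mol worse, power at one-sided 0.05 falls to about 72% with 8% missing and 61% with 30% missing.

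**The case against.** Four points can fairly be made for the plan.

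- **The confirmatory claim is at 12 months.** The hypothesis names no 2-year time point, and not every secondary visit in a non-inferiority trial needs a non-inferiority test. This stands, and it keeps the point at secondary level. A reader might infer that the trial's main conclusion is compromised; nothing in the article supports that.
- **The interval will exist anyway.** A reader might infer that non-inferiority on HbA1c at 2 years could never be assessed. That goes too far: the 24-month confidence interval can be set against 8 mmol/mol. Under the current text, though, that comparison would be post hoc.
- **The authors may have meant the primary analysis to carry over.** Secondary outcomes words the item as the primary outcome at other visits, and the Abstract separates it from the other important secondary outcomes. The margin is also stated for HbA1c without being tied to a visit. But Statistical analyses names 12 months as the dependent variable and makes no exception for the later visit. If carry-over was intended, the sentence needs the same correction.
- **The margin is not automatically valid at 24 months.** The Introduction reports remission falling from 46% at 1 year to 36% at 2 years with face-to-face support, and the article itself lists 8 mmol/mol as a wide margin. If the comparator's effect shrinks, a fixed margin preserves less of it. This stands and is built into the fix.

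**Conclusion.** The point holds for HbA1c at 24 months. The stated rule gives the first-listed secondary outcome a test that does not match the trial's objective, and leaves the 2-year non-inferiority question to a remission test with about 16% to 28% power. With the same sample, HbA1c with an 8 mmol/mol margin would have about 82% to 90% power at one-sided 0.05, or 72% to 84% at one-sided 0.025. These figures rest on SD 13.3 at 24 months, 8% to 30% missing, no true difference, and a margin that remains acceptable at 2 years.

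The 12-month analysis and its sample size are not in dispute. Non-inferiority testing at 2 years is not wholly absent either, since remission has its own margin; what is missing is an adequately powered, pre-specified test. The 6-month visit falls under the same rule, but the consequences described here concern 24 months. This should be corrected, though it does not threaten the primary result.

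**What to change.** Amend the superiority-only sentence in Statistical analyses so that:

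1. HbA1c at 24 months is tested for non-inferiority with the same ANCOVA, confidence level and 8 mmol/mol margin as the primary, and only if the 12-month primary test succeeds.
2. One or two sentences say why 8 mmol/mol still applies at 24 months, given the waning comparator effect.
3. Any superiority tests of HbA1c come after the non-inferiority chain or are labelled supportive. Opening both 12-month superiority and 24-month non-inferiority at full alpha after the primary succeeds would be a branch, not a fixed sequence, and would not protect the error rate. The place of the remission tests relative to this chain should be stated.
4. HbA1c at 6 months is reported with the same interval against the margin, as supportive.
5. Superiority-only testing stays for the remaining secondary outcomes.

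The cost is a few sentences, with no added participants, visits or measurements. The downsides are that the margin has to be defended at 24 months and that the 2-year claim remains secondary. The change should be dated before the 12-month results are known.

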**Trial registration number:**

ClinicalTrials.gov (NCT05491005).

STRENGTHS AND LIMITATIONS OF THIS STUDYA strength of the study is its comparison of eHealth-based calorie restriction for diabetes remission with an active comparator (face-to-face support), rather than with standard care alone.Another strength is that the eHealth programme, specifically developed for this trial, is integrated into the national medical platform ‘Stöd och behandling’ on 1177.se, making it accessible to healthcare providers across Sweden from study start.A limitation of the study is the use of a wider non-inferiority margin for HbA1c of 8 mmol/mol (0.8%), compared with the narrower margin of 4 mmol/mol (0.4%) commonly employed in pharmaceutical trials.

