#### Weight maintenance phase (weeks 19–104)

In this phase, the focus is on maintaining the lower body weight by working on regular meal patterns and goal setting, planning healthy meals, limiting high calorie foods, increasing physical activity, self-monitoring behaviours and dealing with challenges and setbacks. If weight regain occurs during the weight maintenance phase, a rescue plan with diet replacement is recommended, that is, either a period of total diet replacement or replacement of one or two meals a day. Treatment with Orlistat is offered to all participants experiencing difficulty in maintaining weight loss. Despite their potent weight-reducing effects, GLP1 receptor agonists and tirzepatide are not used for weight loss purposes, as they would compromise the ability to determine diabetes remission. However, these medications may be initiated if blood glucose levels rise, as described in the following paragraph.

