#### eHealth support group

All study information and the treatment programme are provided via a digital application and video meetings (online supplemental material 6). The digital programme is available on the Swedish national healthcare platform *1177.se* and contains the information and homework of the therapy programme. The participant has access to the digital application via a mobile phone or PC. New chapters of the therapy programme are made available to the participant during the scheduled video sessions (online supplemental material 4). Participants are equipped with the Omron HN289 scale (Omron Healthcare Co Ltd, Kyoto, Japan), the Accu-Check Instant blood glucose metre (Roche Diabetes Care GmbH, Mannheim, Germany) and the Omron M3 Comfort blood pressure monitor (Omron Healthcare Co Ltd, Kyoto, Japan). Participants measure their body weight, fasting blood glucose and blood pressure every morning and record this on the digital platform. A member of the study team evaluates all daily measurements once a week and gives each participant individual feedback via a message in the digital programme. The study participants can send messages to the study team via this digital platform and receive a response once a week. Participants in the eHealth group have eleven scheduled video support meetings with the study dietitian, study nurse or study doctor (online supplemental material 4). If the daily home measurements show that a participant is not achieving the intended weight loss or maintenance, written feedback is provided by study personnel via the programme’s messaging function. This feedback includes personalised information, such as dietary guidance or a contingency plan involving total diet replacement. Participants are encouraged to respond in order to facilitate the development of a mutually agreed-upon plan. If resolution cannot be achieved through messaging alone, additional contact may be initiated through supplementary video sessions between study staff and the participant. Every second month, study participants measure the HbA1c values at home and send them by post to the laboratory at Umeå University Hospital. The HbA1c result is reported back to the participant via a message in the digital application.

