For the cost-effectiveness analysis, the incremental costs per QALYs gained is the main outcome. Costs include the total diet replacement portions used, meetings with the study team including travel time, time taken by the study team to assess and provide feedback on participants’ measurements each week, other healthcare visits and hospital days, blood glucose-lowering and blood pressure-lowering medications, costs of HbA1c analyses and scales, blood pressure monitors and blood glucose metres. Participants will answer the SF-36 and EQ-5D-5L questionnaires to analyse how they experience their health and quality of life. Costs are analysed based on the intention-to-treat principle. Mean costs are calculated for each group, with cluster-adjusted standard errors for each cost item. Incremental costs per QALY after 2 years are given as the difference in total costs of the groups after 2 years divided by the difference in QALYs. The cost per QALY gained is compared with the Swedish threshold of SEK 500 000. If the ratio is below the threshold, the intervention is categorised as cost-effective. If both interventions are cost-effective, the most effective one is recommended for introduction into normal healthcare.

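### The cost list names no cost for running the eHealth programme, an input of one arm only, and does not cover Orlistat in either arm

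*Protocol article*

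**What the plan says.** The Statistical analyses section of the Protocol article makes cost per QALY gained the main economic outcome and lists the resources that enter it. The list opens with "Costs include the total diet replacement portions used, meetings with the study team including travel time". It goes on to "time taken by the study team to assess and provide feedback on participants’ measurements each week", care sought elsewhere, "blood glucose-lowering and blood pressure-lowering medications", and "costs of HbA1c analyses and scales, blood pressure monitors and blood glucose metres".

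On the eHealth arm, the section on the eHealth support group says: "All study information and the treatment programme are provided via a digital application and video meetings". It adds: "The digital programme is available on the Swedish national healthcare platform". The strengths and limitations box says that "the eHealth programme, specifically developed for this trial, is integrated into the national medical platform". Participants in the face-to-face arm receive the same material on paper at their visits.

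On Orlistat, the section on the weight maintenance phase says: "Treatment with Orlistat is offered to all participants experiencing difficulty in maintaining weight loss".

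The secondary hypothesis (Objective) is that eHealth is the more cost-effective form of support. The ratio is judged against SEK 500 000 per QALY and feeds a recommendation for routine care.

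**The concern.** The content of the treatment programme is the same in both arms, and only the method of support differs. The incremental cost is therefore largely the cost of the support method. The list is detailed enough to name bathroom scales, yet it has no line for the digital programme, which only the eHealth arm uses. Leaving out a cost carried by one arm shifts the comparison in one direction, here towards the stated hypothesis.

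If the arms have similar outcomes, as the non-inferiority hypothesis expects, the QALY difference will be small and the economic conclusion will rest mainly on the cost difference. Even a modest missing item could then matter. The conclusion is also meant to guide adoption in routine care, where operating and supporting the programme uses real resources.

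Orlistat raises a different and weaker issue. It is a treatment the protocol provides for, but it is neither a glucose-lowering nor a blood-pressure-lowering drug in the sense of the list. As written, its cost is not captured in either arm.

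**Working it through.** The article states no unit cost and no cost total, so there is no figure to reproduce. The check compares the list with the resources described elsewhere, then works out direction and possible size.

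**1. List against resources**

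- Meetings: 33 scheduled visits (face-to-face) and 11 scheduled video meetings (eHealth), a difference of 33 − 11 = 22. The item is not limited to one arm, so both are counted.
- Weekly review of home measurements and written feedback: eHealth. Counted.
- Scale, glucose meter and blood pressure monitor: supplied to each eHealth participant, used at the visits in the other arm. Counted.
- HbA1c analyses: every second month at home in eHealth, in addition to the study visits. Counted.
- Glucose- and blood-pressure-lowering drugs: both arms. Counted.
- Digital programme (use, maintenance, technical support): eHealth only. **Not named.**
- Orlistat: both arms. **Not named.**
- Printed chapters and reminder telephone calls (face-to-face) and the pedometer (both arms): not named, probably small.

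**2. Direction for the digital programme**

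Let p ≥ 0 be the programme's running cost per eHealth participant. The listed cost difference (eHealth minus face-to-face) equals the full difference minus p. Since p cannot be negative, the omission can only make eHealth look cheaper, or leave the result unchanged if p = 0.

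**3. Direction for Orlistat**

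The error in the cost difference is (Orlistat cost per participant in eHealth) − (Orlistat cost per participant in face-to-face). The documents do not say which arm will use more, so the sign is unknown.

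**4. Possible size of p (all inputs assumed except the threshold and the sample size)**

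- QALY equivalent at the threshold, p / 500 000: for SEK 1 000, 1 000 / 500 000 = 0.002; for SEK 5 000, 5 000 / 500 000 = 0.010 QALY per participant.
- Shift in the ratio, p / (QALY difference), for an assumed absolute difference of 0.05 to 0.005: with SEK 1 000, 1 000 / 0.05 = SEK 20 000 to 1 000 / 0.005 = SEK 200 000 per QALY; with SEK 5 000, SEK 100 000 to SEK 1 000 000 per QALY.
- Dependence on how a fixed cost is spread. With 106 / 2 = 53 participants per arm, an assumed SEK 100 000 is 100 000 / 53 ≈ SEK 1 890 each, and SEK 2 000 000 is about SEK 37 740 each. Spread over an assumed 5 000 users, the same sums are SEK 20 and SEK 400 each.

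Against a threshold of SEK 500 000 per QALY, the effect runs from negligible to decisive, depending on figures the article does not give.

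**The case against.** The strongest reply is that the sentence begins by saying what costs include and does not claim to be complete. The article condenses a fuller plan, and the economic analysis will be reported separately after the 24-month follow-up. Nothing says that programme costs are excluded, and some minor face-to-face resources are also unnamed, which suggests a summary. This has weight: it means that an actual exclusion is not established. It does not dispose of the point, because the authors chose to print a list that goes down to small devices and passes over an input specific to one arm. If the item is already intended, one phrase settles it.

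A second reply is that the platform exists nationally, so the marginal cost may be close to nil, and that treating development as sunk is a legitimate choice of perspective if declared. That stands, and it limits the size of the point.

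A reader might go further and infer that the list as a whole counts face-to-face contact in full while sparing eHealth. The documents do not support that. Video meetings are counted on the same terms, and weekly feedback time, home devices and the extra HbA1c tests fall mainly on eHealth and are also counted. Nor do they support reading the Orlistat gap as a bias towards eHealth, since the drug is available in both arms.

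**Conclusion.** The point holds in a limited form. The list names no cost for using, maintaining or supporting the digital programme, which only the eHealth arm uses. Applied as listed, it understates eHealth cost. The direction is certain if the programme has any running cost at all, but the amount cannot be quantified from the documents and may be small. The SEK and QALY figures in the working are illustrations under assumed inputs, not estimates of bias.

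It would be tempting to express the omission as a share of the saving from 22 fewer meetings. That would not be sound: the article gives no cost per meeting, and the net cost difference also contains travel time, weekly review, devices and HbA1c tests.

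The absence of Orlistat is a separate completeness gap with no known direction. Both are worth correcting because the correction is cheap and the economic results are not due until after the 24-month follow-up.

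**What to change.** Add two items to the cost list.

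1. The per-participant cost of running, maintaining and supporting the eHealth programme. If the marginal cost is truly nil, enter it as zero, give the reason, and vary it over a stated range in a sensitivity analysis. Bring in development cost only as a declared scenario, with the assumed number of users stated.
2. Orlistat use in both arms, costed in the same way as the other drugs.

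The cost is one request to the platform owner for a unit cost, collection of Orlistat use, and a change of wording. The article lists only the numbers of antidiabetic and antihypertensive prescriptions as outcomes, so it should not be assumed that Orlistat use is already captured. The downside is that the result may turn out slightly less favourable to eHealth.

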### Randomisation

After the initial examination, participants are randomised in a 1:1 ratio to either the eHealth support group or the face-to-face support group (table 1). Randomisation is performed using permuted blocks with random sizes of 2, 4 or 6 and is stratified by study centre. The allocation sequence is generated by the statistician PL and uploaded to the *Research Electronic Data Capture (REDCap*). On completion of all baseline assessments, a nurse retrieves the participant’s group assignment from *REDCap* and notifies the participant.

**Table 1 T1:** Timetable of enrolment, interventions and assessments for the eHealth DIabetes remission Trial (eDIT)

Timepoint	Study period					
	Enrolment	Allocation	Post-allocation			
	-t_1_	0	Diet start	6 months	12 months	24 months
Enrolment						
Eligibility screen	X					
Informed consent	X					
Allocation		X				
Interventions						
eHealth support group						
Face-to-face support group						
All participants: Weight loss intervention						
Assessments						
HbA1c	X			X	X	X
Anthropometry*	X			X	X	X
Blood pressure	X			X	X	X
Plasma lipid profile and liver enzymes	X			X	X	X
Fasting glucose and OGTT	X			X	X	X
Questionnaires†	X			X	X	X
Health economic evaluation						X

This table is adapted from the SPIRIT 2013 statement.^9^

* Anthropometry = body weight, waist circumference, hip circumference, abdominal height.

† Questionnaires: EuroQol Quality - 5 Dimensions - 5 Levels (EQ-5D-5L), Brunnsviken Brief Quality of Life Scale, 36-Item Short Form Survey (SF-36), three factor eating questionnaire, Karolinska Exhaustion Disorder Scale and food frequency questionnaire 2020.

HbA1c, haemoglobin A1c; OGTT, oral glucose tolerance test.

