At the beginning and after 6, 12 and 24 months, the study participants undergo the following examinations (table 1): Body weight is measured to the nearest 100 g using a Tanita WB-100 MA scale (Tanita Cooperation, Tokyo, Japan) at the Umeå study site and a SECA 704 scale (seca, Hamburg, Germany) at the Jönköping study site while fasting, wearing light clothing and no shoes. One kilogramme is deducted for clothing. Height is measured to the nearest mm with a Seca 264 at the Umeå study site and with a Seca 216 (both seca, Hamburg, Germany) at the Jönköping study site. Waist circumference is measured to the nearest mm at the end of a normal exhalation with a tape measure in the horizontal plane midway between the iliac crest and the lowest rib. The abdominal height is measured in the supine position as the distance between the highest point of the abdomen and the hard surface below it after a normal exhalation using a sagittal abdominal measuring device (AJ Medical, Lidingö, Sweden). Blood pressure at the research facilities is measured on the right upper arm after 5 min of rest in a sitting position using a Welch Allyn 3400 blood pressure monitor (Welch Allyn, Skaneateles Falls, USA). Blood pressure is measured three times, and the average of the last two measurements is reported. Home blood pressure monitoring is performed over a 24-hour period using the OnTrak device (Spacelabs Healthcare, Snoqualmia, WA, USA). Venous blood samples for HbA1c, fasting glucose, plasma lipid profile and plasma liver enzymes are analysed at the hospital laboratory closest to the study site. Additionally, venous blood samples are collected in the fasting state and at 30, 60, 90 and 120 min following the OGTT. These samples are stored at −80°C for future, as yet unspecified, analyses. Data regarding daily steps will be collected using the GRV fitness tracker non-Bluetooth fitness watch (GRV, USA). Participants answer the EQ-5D-5L and the Brunnsviken Brief Quality of Life Scale to assess their quality of life,^22 23^ the SF-36 questionnaire to assess their health,^24^ the 21-item three-factor eating questionnaire to investigate their relation to food,^25^ the Karolinska Exhaustion Disorder Scale to estimate exhaustion^26^ and the validated food frequency questionnaire 2020 to assess their eating habits.^27^ At the end of the study, participants answer 15 open questions about their study experience. All questionnaires and questions are answered directly in *REDCap* using a tablet, smartphone or computer.

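### The incremental cost per QALY is specified without covariates, although baseline EQ-5D-5L and centre are recorded; adjusting for them would remove avoidable variance at no cost

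*Protocol article*

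**What the plan says.** Cost-effectiveness is the second of the trial's two hypotheses (Objective). Under Statistical analyses the article states: "For the cost-effectiveness analysis, the incremental costs per QALYs gained is the main outcome". The calculation follows in two steps. First, "Mean costs are calculated for each group, with cluster-adjusted standard errors for each cost item". Then comes the ratio, with QALYs in the denominator: "Incremental costs per QALY after 2 years are given as the difference in total costs of the groups after 2 years divided by the difference". The ratio is compared with SEK 500 000, and an intervention below that value is called cost-effective. No covariate is named for costs or for QALYs.

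In the same section, the HbA1c model is given covariates and a reason for them: "The analysis will be adjusted for baseline HbA1c and study centre to account for stratified randomisation". The stratification itself is described under Randomisation, where allocation "is stratified by study centre".

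The data for an adjusted QALY analysis are already planned. Study procedure and data collection says: "At the beginning and after 6, 12 and 24 months, the study participants undergo the following examinations", and the list that follows includes EQ-5D-5L. Table 1 shows the same times for the questionnaires.

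**The concern.** If QALYs are built in the usual way, as the area under each participant's utility curve, baseline utility enters the 2-year total directly. It also correlates with the later utilities that make up the rest of the total. A chance difference in baseline utility between two arms of about 53 is then carried into the figure reported as QALYs gained, although it existed before treatment.

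The two arms receive the same programme by different routes, so a small true QALY difference is plausible, though the article does not say so. If it is small, noise in the denominator matters, because the cost-effectiveness label is attached to the ratio itself. At stake is needless imprecision in the main result of the second hypothesis. A second risk is that, if the choice stays open, it could be made after a baseline imbalance has been seen.

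**Working it through.** **The plan's own figures.** The article gives no utility SD, no correlation between visits and no precision for the ratio, so there is no stated figure to reproduce on this point. The only design figure used is the sample size. It reproduces at one-sided alpha 0.05: 2 × (1.645 + 1.282)² × 13.3² / 8² = 47.3, rounded up to 48 per arm, or 96 in total. Adding 10% gives 96 × 1.1 = 105.6, or 106, hence 53 per arm.

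**Assumptions, none from the article.**
- The QALY is the trapezoidal area under EQ-5D-5L utility at 0, 0.5, 1 and 2 years.
- Utility has the same SD at every visit; range 0.10 to 0.25.
- The correlation rho is equal between all visits; range 0.2 to 0.8.
- All 53 per arm have data.

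**Weights.** The trapezoidal rule gives 0.25, 0.50, 0.75 and 0.50, which sum to 2.0. The sum of squares is 0.0625 + 0.25 + 0.5625 + 0.25 = 1.125.

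**Formulas.**
- Slope of QALY on baseline utility: b = 0.25 + 1.75 × rho
- Variance of the QALY in units of SD²: V = 1.125 × (1 − rho) + 4 × rho
- Share of variance removed by adjustment: R² = b² / V
- Ratio of adjusted to unadjusted standard error: √(1 − R²)

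| rho | b | V | R² | SE ratio |
|---|---|---|---|---|
| 0.2 | 0.600 | 1.7000 | 0.21 | 0.89 |
| 0.5 | 1.125 | 2.5625 | 0.49 | 0.71 |
| 0.8 | 1.650 | 3.4250 | 0.80 | 0.45 |

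At rho 0.5 the standard error therefore falls by about 29%. For utility SD 0.20, for example, it goes from 0.20 × √(2.5625 × 2/53) = 0.062 to 0.062 × 0.71 = 0.044.

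**Other correlation structure.** If correlation instead decays with time (first-order autoregressive, rho per year), R² is 0.30, 0.46 and 0.65 at rho 0.3, 0.5 and 0.7. Equal correlation gives 0.30, 0.49 and 0.69. The result does not hinge on the equal-correlation assumption.

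**Effect of one chance imbalance.** The standard error of the baseline difference is SD × √(2/53). The shift in the unadjusted QALY difference is b times that, with b = 1.125 at rho 0.5.
- SD 0.10: 0.0194 × 1.125 = 0.022
- SD 0.25: 0.0486 × 1.125 = 0.055

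The part that comes only from the baseline weight of 0.25 is smaller: 0.25 × 0.0194 = 0.005 to 0.25 × 0.0486 = 0.012. The rest comes through the assumed correlation with later visits.

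No figure is offered for centre adjustment of costs or QALYs, because the article has nothing to base one on.

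**The case against.** The strongest objection is that the quoted sentence is the generic definition of an incremental cost-effectiveness ratio. It never says that the difference is unadjusted and would fit an adjusted one equally well. The article gives covariates only for its primary outcome, so their absence here may be brevity. The health-economic results are to be published separately after 24 months, and a fuller plan, not shown, may specify the adjustment.

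Much of this stands. A reader might infer that the plan has deliberately fixed an unadjusted analysis, and the text does not establish that. What remains is narrower: the section sets out a calculation step by step from group mean costs, names no covariate, and comes after a paragraph that writes out adjustment for HbA1c. Someone following it as written would produce an unadjusted ratio. The mention of cluster-adjusted standard errors does not change this, since it concerns the uncertainty of cost items and not the differences themselves.

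Other stronger readings also go beyond the documents:
- A reader might say that half of the precision is lost. That figure needs a correlation near 0.5, which the article does not give, and refers to variance. The standard error falls by about 29% there.
- A reader might carry the figures over to the ratio. They describe the QALY difference only. The uncertainty of the ratio also depends on costs and on how near the QALY difference lies to zero.
- A reader might speak of lost power. The cost-effectiveness paragraph compares a ratio with a threshold and describes no significance test of the QALY difference.
- A reader might call the result biased. Under randomisation, chance imbalance adds variance and no systematic error.

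**Conclusion.** The point holds as a free improvement, not as an error that invalidates the analysis. As written, the calculation leaves the QALY difference unadjusted although a strongly related baseline measure and the stratification factor are both recorded. That unadjusted reading is the natural one, not stated text.

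How much variance is avoidable cannot be fixed from the article. The 21% to 80% range is wide because the correlation is unknown, and it depends on the trapezoidal EQ-5D-5L construction. The article names both EQ-5D-5L and SF-36 and does not say which supplies the utility. Even at the low end of the range, about a fifth of the variance of the QALY difference would be removed.

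**What to change.** In the cost-effectiveness paragraph of Statistical analyses, or by confirmation in the health-economic analysis plan if it already covers this:
- Define the incremental QALY as the group coefficient from a regression of 2-year QALY on group, baseline EQ-5D-5L utility and study centre.
- Define the incremental cost as the group coefficient from a regression of 2-year cost on group and study centre.
- Form the ratio from these two adjusted differences and report the unadjusted ratio alongside.

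This should be settled before the 24-month data are analysed, so that the choice cannot depend on an observed imbalance. It costs a few lines of wording. It needs no new data, visits or participants, because baseline EQ-5D-5L and centre are already collected.
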